**Belo Horizonte**  
**Universidade Federal de Minas Gerais**  
**Escola de Educação Física, Fisioterapia e Terapia Ocupacional**  
**Department of Physiotherapy**  
**2023**

## 1. INTRODUCTION

Stroke is a health condition that has a high burden throughout the world, especially in underdeveloped and developing countries, such as Brazil (Feigin et al., 2021). This high burden is associated with the high incidence and prevalence of this health condition and the important disabilities that compromise the health and well-being of individuals (Feigin et al., 2021, Damsbo et al., 2020, Carvalho-Pinto et al., 2016). More than 12 million new cases of stroke occur annually, and it has been estimated that one in four people over the age of twenty-five will suffer an episode of stroke during their lifetime (Feigin et al., 2022). Currently, there are more than 100 million people surviving strokes in the world, 67% of whom are under 70 years of age (Feigin et al., 2022). Furthermore, it has been identified that, annually, more than 143 million years of healthy life are lost due to stroke-related deaths and disabilities (Feigin et al., 2022).

Another contributing factor to the high burden of stroke worldwide is its recurrence (Feigin et al., 2021, Lin et al., 2021). Recurrent stroke has a high incidence and prevalence, is considered the main cause of hospital readmissions during the first year after the stroke episode, results in an even more severe disability, and consequently, more impaired health, well-being and quality of life when compared to individuals who suffered an episode of stroke, and contributes to an increase of approximately 40% in healthcare costs (Lin et al., 2021, Wang et al., 2016, Zhong et al., 2016, Modrego et al., 2000). These facts point to an important public health need: actions for stroke secondary prevention. This need has been identified by the Stroke Association and James Lind Alliance, which identified stroke secondary prevention as one of the top 10 priority research areas to reduce the burden of stroke (Stroke Association and James Lind Alliance, 2021). Furthermore, this priority became even more evident in the context of the Corona Virus Disease-19 (COVID-19) pandemic, which compromised the rehabilitation process of individuals post-stroke (Cadilhac et al., 2021).

Guidelines state that the rehabilitation process for individuals post-stroke should aim to keep them well and free from additional events (Gittler et al., 2018, Winstein et al., 2016). These guidelines also highlight the importance of including interventions aimed at adopting a healthy lifestyle in stroke secondary prevention programs (Gittler et al., 2018, Winstein et al., 2016). Specific guidelines on stroke secondary prevention, in addition to guiding the adoption of a healthy lifestyle, also recommend the implementation of multimodal intervention programs (Gladstone et al., 2021, Kleindorfer et al., 2021). Multimodal intervention programs may include, for example, health

education actions related to medication adherence, knowledge about stroke and risk factors for the occurrence of stroke, and increasing the practice of physical activity (Lawrence et al. , 2015). However, despite recent guidelines and recommendations, the implementation of actions for stroke secondary prevention is still infrequent.

Recently, the concept of stroke secondary prevention based on non-surgical and non-pharmacological interventions was defined using the Delphi method (Lawrence et al., 2019). This definition addresses improving health and well-being, as well as reducing the risk of recurrent stroke, based on the implementation of theoretically-informed interventions and educational strategies (Lawrence et al., 2019). Furthermore, the concept presented guides that interventions aimed at managing risk factors related to lifestyle must be contextualized and individualized considering the capabilities, needs and priorities of individuals, as well as their families (Lawrence et al., 2019). Managing the set of risk factors related to lifestyle, such as smoking, harmful alcohol consumption, inadequate diet and physical inactivity, has been considered the cornerstone of stroke secondary prevention strategies (Gladstone et al., 2021, Kleindorfer et al., 2021, PAHO, 2020).

Management of this set of risk factors has been considered the cornerstone of stroke secondary prevention strategies because behavioral risk factors represent approximately 47% of the stroke burden (Feigin et al., 2022). In addition to the direct benefits achieved by its management, indirect benefits related to the management of cardiovascular risk factors can also be identified (Gladstone et al., 2021, Kleindorfer et al., 2021, PAHO, 2020). Cardiovascular risk factors include, for example, high blood pressure, dyslipidemia, hypercholesterolemia and diabetes (Feigin et al., 2022, Gladstone et al., 2021, Kleindorfer et al., 2021, PAHO, 2020). However, to better target the implementation of actions for stroke secondary prevention, it is important to consider, as previously pointed out, that these actions must be contextualized and individualized considering the capabilities, needs and priorities of individuals, as well as their families (Lawrence et al ., 2019).

There are still few studies that detail the Brazilian context regarding the profile of adoption of healthy lifestyle behaviors related to the pillar of stroke secondary prevention strategies: smoking cessation, safe alcohol consumption, adequate diet and regular physical activity. Ribeiro et al. (2012), in one of the few studies developed on this topic in Brazil, showed that, of the 140 individuals post-stroke living in João Pessoa-PB included in the study, 79% did not consume alcoholic beverages and 84% were not smokers. Trabaquini (2015) showed that, of the 30 individuals post-stroke living in

Andirá-PR included in the study, 70% never smoked, 17% stopped smoking and 13% were smokers; 60% never consumed any type of alcoholic beverage, 30% stopped consuming it and 10% still consumed it socially; 93% consumed fruits, vegetables and legumes; and 77% did not practice any type of physical activity. Muller (2015) showed that, of the 407 individuals post-stroke living in Joinville-SC included in the study, 22% were smokers and 48% had never smoked. Furthermore, Lopes et al. (2022) showed that, of the 50 individuals post-stroke living in Belo Horizonte-MG included in the study that is still ongoing, 86% did not smoke, 76% did not consume alcoholic beverages, 68% stated that they had adequate diet, 62% consumed 2-3 fruits/vegetables/day; and only 36% practiced physical activity. As can be seen in these Brazilian studies, regular physical activity is the healthy lifestyle behavior least adopted by individuals post-stroke.

Several benefits related to the management of risk factors are associated with the regular practice of physical activity by individuals post-stroke, such as, for example, the reduction of mortality, blood pressure, cholesterol levels and blood glucose levels (Billinger et al., 2014, Prior et al., 2017, D'Isabella et al., 2017, Loprinzi, 2015, Saunders et al., 2014). Furthermore, recently, Lennon et al. (2021) investigated the predictors of adherence to lifestyle recommendations for stroke secondary prevention and identified that the variable cardiovascular fitness (measure operationalized as peak oxygen consumption,  $VO_{2peak}$ ) was the only significant predictor of adherence to three health behaviors: healthy diet, physical activity and smoking cessation. Improved cardiovascular fitness is achieved through regular physical activity (Billinger et al., 2014). Therefore, these findings reinforce the importance of encouraging regular physical activity by individuals post-stroke when aiming to also improve adherence to other healthy behaviors. However, despite these benefits already described and considering the data presented previously, it has been identified that individuals post-stroke do not adopt the behavior of regular physical activity (Billinger et al., 2014).

Several barriers have been identified regarding individuals post-stroke not engaging in regular physical activity (Billinger et al., 2014). Some examples include: lack of interest or motivation, and lack of perceived self-confidence and self-efficacy (Billinger et al., 2014). Furthermore, a lack of knowledge about how and where to exercise and the potential benefits of physical activity has also been identified (Billinger et al., 2014). These barriers point to the need for actions that are contextualized and individualized, considering the capabilities, needs and priorities of individuals. A fact that has already been guided in the literature (Lawrence et al., 2019). To overcome these

barriers, it is important that theoretically-informed strategies are implemented (Lawrence et al., 2019).

Studies on strategies for changing the behavior of individuals post-stroke to adopt healthy behaviors, including regular physical activity, have currently been carried out (Bridgwood et al., 2018, Heron et al., 2017, Katsanos et al., 2017, Lennon et al., 2014, Lager et al., 2014). However, it is important to consider that behavior change interventions are typically complex and involve several interactive components (Craig et al., 2008). As a result, these interventions can be difficult to implement and replicate both in research and clinical practice (Michie et al., 2015). Therefore, there is a need to implement theoretically-informed strategies, aiming for a greater possibility of achieving the expected results, and adequate replication of interventions both in research and clinical practice (Michie et al., 2015). In this sense, Michie et al. (2015) developed a taxonomy for reporting and describing behavior change interventions. However, the use of theoretically-informed strategies for stroke secondary prevention aimed at adopting healthy lifestyle behaviors is not evident.

A recently published scoping review examined national guidelines for the care of individuals post-stroke and audit documents across all World Health Organization (WHO) regions to identify recommendations for non-surgical and non-pharmacological interventions for stroke secondary prevention and associated performance indicators (Hall et al., 2022). The authors found that these interventions for stroke secondary prevention are not a current pillar in national guidelines for the care of individuals post-stroke and audit documents (Hall et al., 2022). This scenario is even more serious considering underdeveloped and developing countries, such as Brazil, where fewer guidelines and documents were identified (Hall et al., 2022). Therefore, despite recent recommendations and guidelines for implementing theoretically-informed behavior change techniques for stroke secondary prevention, this has possibly not been applied in research and clinical practice worldwide. Furthermore, this scoping review showed that, of the 16 guidelines and documents identified, 11 recommended the practice of physical activity (Hall et al., 2022). However, the guidelines are still shallow, and no guidelines for treatment or stroke secondary prevention were found that provided specific guidelines for prescribing physical activity in Brazil (Hall et al., 2022). Therefore, in the Brazilian context, individuals post-stroke should still receive general guidelines for regular physical activity, which may not be effective in resulting in an increase in the level of physical activity in this population.

The Pan American Health Organization (PAHO) recently published a technical package called HEARTS for the management of cardiovascular diseases, including a specific document containing guidelines for adopting healthy behaviors, translated into Brazilian Portuguese (OPAS, 2019). This technical package consists of six modules that correspond to each of the letters of the HEARTS acronym (OPAS, 2019). Module H, “Healthy-lifestyle”, which includes patient counseling (OPAS, 2019). Module E, “Evidence”, which comprises the use of evidence-based protocols (OPAS, 2019). Module A, “Access”, which comprises access to essential medicines and technologies (OPAS, 2019). The R module, “Risk”, which comprises risk-based management of cardiovascular diseases (OPAS, 2019). The “T” module, which comprises team “Team” as the basis for care (OPAS, 2019). And, finally, module “S”, “Systems for monitoring” (OPAS, 2019).

In this technical package, the four main behavioral risk factors for cardiovascular diseases are described: unhealthy diet, smoking, harmful alcohol consumption and insufficient physical activity (OPAS, 2019). For healthy levels of physical activity for adults, the HEARTS technical package highlights the guidance that all individuals, including individuals post-stroke, perform at least: 150 minutes of moderate physical activity or at least 75 minutes of vigorous physical activity, distributed throughout the week; or an equivalent combination of moderate and vigorous activity; or muscle strengthening activities, exercising large muscle groups on two or more days of the week (OPAS, 2019).

The HEARTS technical package presents aspects related to behavior change and presents the brief intervention model using the 5As tool: ask, advise, assess, assist and arrange (OPAS, 2019). The use of this tool is recommended to encourage behavioral changes (OPAS, 2019). Considering the taxonomy for behavior change techniques proposed by Michie et al. (2013), the HEARTS technical package addresses those called goals and planning, feedback and monitoring, and social support (OPAS, 2019). To date, no study has been identified that used this HEARTS technical package to increase the level of physical activity in individuals post-stroke

In Brazil, only one clinical trial was identified in Clinical Trials with the objective of promoting physical activity in individuals post-stroke (Scianni, 2022). This clinical trial is being carried out with individuals post-stroke in the acute and subacute phase using theoretically-informed strategies (Scianni, 2022). However, guidelines recommend that physical activity should be a component of the ongoing care of individuals post-stroke (Billinger et al., 2014). In this sense, it is also necessary to promote the practice of

physical activity with individuals post-stroke in the chronic phase, using theoretically-informed strategies. Furthermore, no study was found that used the HEARTS technical package with the aim of increasing the level of physical activity in individuals post-stroke. Considering that this HEARTS technical package was translated into Brazilian Portuguese, its use can contribute to achieving significant results. Finally, the literature has also been scarce regarding the promotion of physical activity with individuals post-stroke in the chronic phase using a combination of strategies, such as the use of pedometers associated with another strategy (Lynch et al., 2018).

In addition to identifying the need to encourage the practice of physical activity by individuals post-stroke, it is important to ensure that this practice is continuous (Billinger et al., 2014). A possible strategy that can contribute to solving this problem is the use of telehealth. Telehealth refers to the provision of rehabilitation services in a remote location using information and communication technologies (Brennan et al., 2009). The use of telehealth interventions has been adopted in the health care of individuals post-stroke and has become more frequent with the COVID-19 pandemic (Bloem et al., 2020). Theoretically-informed interventions for self-management of lifestyle-related risk factors with individuals post-stroke, such as to increase physical activity level (Lawrence et al., 2019), can be delivered remotely via telehealth (Gladstone et al., 2022). However, recommendations for the use of telehealth interventions for behavior change and self-management in stroke secondary prevention are based on evidence classified as level C (Gladstone et al., 2022). Therefore, it is necessary to investigate the effect of interventions to increase the level of physical activity of individuals post-stroke via telehealth to better recommend the literature regarding the use of this intervention.

## 1.1 OBJECTIVES

**Primary objective:** To investigate whether a theoretically-informed telehealth intervention involving the HEARTS technical package and the use of an activity monitor to increase physical activity level is feasible to implement with individuals post-stroke.

**Secondary objective:** Estimate the parameters for carrying out a randomized clinical trial (RCT) considering the outcomes level of physical activity and number of individuals post-stroke who became physically active, systolic blood pressure (SBP) and diastolic blood pressure (DBP), cardiorespiratory fitness, self-efficacy for physical activity and health-related quality of life.

## 1.2 Study hypotheses

H0: A theoretically-informed telehealth intervention involving the HEARTS technical package and the use of an activity monitor to increase the level of physical activity is not feasible to implement with individuals post-stroke.

H1: A theoretically-informed telehealth intervention involving the HEARTS technical package and the use of an activity monitor to increase the level of physical activity is feasible to implement with individuals post-stroke.

## 2. METHODOLOGY

### 2.1 Design

This is a phase 1 feasibility study to conduct an RCT (Eldridge et al., 2016), with a blinded evaluator and concealed allocation. The project will be submitted to the Research Ethics Committee of the Universidade Federal de Minas Gerais (UFMG). The cover page is attached (ANNEX 1). All necessary consents for the development of the study were obtained (ANNEX 2). Furthermore, this project was approved by the UFMG Physiotherapy Department chamber (ANNEX 3).

This study will be registered at [www.ClinicalTrials.gov](http://www.ClinicalTrials.gov) and carried out in accordance with CONSORT extension recommendations for pilot or feasibility studies (Eldridge et al., 2016). Recruitment of individuals and data collection will begin after approval by the Research Ethics Committee of the UFMG.

All individuals will be instructed on the procedures that will be carried out and will only be included after agreeing to voluntary participation and signing the Informed Consent Form (ICF) (APPENDIX 1).

### 2.2 Participants

A convenience sample will be recruited in the community of the city of Belo Horizonte, through contact with outpatient clinics, clinics, hospitals, health centers, associations, research groups and extension projects developed with the population of interest.

To participate in the study, individuals must meet the following inclusion criteria:

- Present a clinical diagnosis of stroke more than six months ago;
- Be 18 years old or over;
- Be classified as “Inactive” according to the Adjusted Activity Score (AAS) of the Human Activity Profile (HAP) (Souza et al., 2006);

- Be able to walk 10 meters independently with or without a walking aid (considering that walking is a potential way to participate in physical activity);
- Present medical clearance to practice physical activity.

The following individuals will be excluded:

- Those who test positive for possible cognitive impairment (Mini-Mental State Examination) using the cutoff point based on educational level (Bertolucci et al., 1994) and/or have comprehension aphasia, assessed by the ability to respond to verbal commands using body movements (“raise your unaffected arm and open your hand”) (Teixeira-Salmela et al., 2007);
- Those with the presence of pain or other adverse health conditions that compromise the implementation of the proposed intervention program, such as vestibular disorders, severe arthritis, or any other diagnosed nervous system disease.

### **2.3 Randomization and concealed allocation**

Participants will be allocated into two groups (experimental and control). The allocation sequence will be generated by a website ([www.randomization.com](http://www.randomization.com)). A research assistant, who will not be involved in recruitment, will perform the randomization and place the sequence in opaque, numbered, sealed envelopes. Envelopes will be prepared prior to the start of the study by a research assistant not involved in the research. Each participant will be allocated to one of the groups respecting the contents inside the envelopes. To minimize possible bias resulting from participants not being blinded, they will be instructed not to comment to the examiner about the group to which they were assigned.

### **2.4 Intervention**

Participants will undergo an intervention program involving the HEARTS technical package (OPAS, 2019) and the experimental group will have the addition of self-monitored physical activity using the Smartwatch Mi Band 7®. Therefore, the only difference between the groups is that participants in the control group will not receive the physical activity monitor (Smartwatch Mi Band 7®). To monitor adherence to the protocol, individuals will receive a diary of regular physical activity, which will be filled

out, for each day of physical activity, the duration and the subjective effort score according to the Modified Borg Categorical Scale (Borg, 1982, Cavallazzi et al., 2008) (APPENDIX 2). The researcher responsible for implementing the intervention (physiotherapist with previous experience in caring for individuals post-stroke and one of the researchers responsible for the present study) and a research assistant (scientific initiation students from the undergraduate physiotherapy course) will be trained in advance for standardization. implementation of intervention protocols, which will always be carried out by the same therapist. A companion/caregiver will be instructed to assist the individual in filling out the diary, if necessary.

#### **2.4.1 Experimental group**

Participants in the experimental group will carry out an intervention program involving the HEARTS technical package (OPAS, 2019) and the practice of self-monitored physical activity. The HEARTS technical package presents the model for implementing the 5As brief intervention to increase physical activity (OPAS, 2019). This method involves: ask, advise, assess, assist and arrange (OPAS, 2019). Participants in the experimental group will receive a physical activity monitor (Smartwatch Mi Band 7®) (as instructed in the “assist” topic in the HEARTS technical package) and will be monitored by telephone, once a week, aiming to identify successes and difficulties, as well as, to reinforce successes and identify solutions to identified difficulties (as guided in the “arrange” topic in the HEARTS technical package) (PAHO, 2019). These individuals will undertake a 12-week intervention program. In the first week, individuals will carry out the first four stages of the 5As brief intervention in a meeting that will be held in person at the participant's home or at the Laboratório de Estudos em Reabilitação Neurológica do Adulto (NEUROLAB) at Escola de Educação Física, Fisioterapia, e Terapia Ocupacional (EEFFTO) (UFMG), depending on the participant's availability, where they will be instructed on how to use the physical activity monitor (they will be instructed to use it during the time they are awake, every day, during the study), they will receive the diary of regular physical activity practice (presented in the previously developed evaluation form, APPENDIX 2), will be guided on how to fill it out, and will schedule the best times to receive the weekly telephone call.

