## **2.5 Measurement of outcomes**

The measurement of primary and secondary outcomes will be carried out in NEUROLAB. Measurements will be carried out at the initial assessment (week 0), immediately after the end of the intervention program (week 12) and one month after the end of the intervention program (week 16). In the initial assessment (week 0), clinical and demographic data will be collected from all individuals for the purpose of verifying the eligibility criteria, identification and characterization of the sample. For this, a previously developed evaluation form will be used (APPENDIX 2). In weeks 12 and 16, a previously developed reassessment form similar to the evaluation form will be used, in addition to the addition of an assessment of the participant's satisfaction with the intervention carried out (APPENDIX 3). This collection will be carried out by a previously trained examiner, blinded to group allocation. All participants will be instructed not to comment on information about the training received.

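### The smartwatch that alone separates the groups is to be used all waking hours, with no exception for visits to the blinded examiner

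*Protocol*

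**What the plan says.** The protocol treats the watch and the examiner in separate places.

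- **Wear.** Section 2.4.1 says of the experimental group that "they will be instructed to use it during the time they are awake, every day, during the study". It makes no exception for assessment days.
- **What separates the groups.** Section 2.4 states that "the only difference between the groups is that participants in the control group will not receive the physical activity monitor". Section 2.4.2 repeats that controls have the same programme without the watch.
- **Blinding.** Section 2.1 describes the study as one "with a blinded evaluator and concealed allocation". Section 2.5 adds: "This collection will be carried out by a previously trained examiner, blinded to group allocation". Section 2.7 has one evaluator collect all the data and again states blinding to allocation.
- **Where and when.** Section 2.5 says: "The measurement of primary and secondary outcomes will be carried out in NEUROLAB". Visits are at weeks 0, 12 and 16. Week 12 comes directly after the programme ends, and week 16 a month later.
- **Safeguards.** Section 2.3 says of participants that "they will be instructed not to comment to the examiner about the group to which they were assigned". Section 2.5 adds a similar request about the training they received. No other safeguard is given.
- **Reassessment form.** At weeks 12 and 16 the form also includes an "assessment of the participant's satisfaction with the intervention carried out".

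**The concern.** Participants know their group, and section 2.3 accepts this. The examiner is therefore the one person in contact with participants at outcome assessment who can be kept blind. A request not to speak does not hide an object on the wrist. If that object is the only thing that differs between the groups, a participant who obeys the wearing instruction may disclose the allocation simply by arriving.

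At stake are the measures on which an examiner can have some influence. The secondary objective is to estimate parameters for a later randomized trial, and section 2.8 plans between-group effect sizes. An examiner who knows the group may prompt, interpret or read differently, and those estimates would carry that into the design of the next trial. The feasibility study would also hand on a blinding procedure with a known gap.

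**Working it through.** No arithmetic applies. The point depends on no error rate, effect size or variance, and section 2.6 makes no formal sample size calculation. The check is to follow one experimental participant through the plan.

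1. **Week 0.** The baseline visit is not affected. The watch is given at the first intervention meeting, after allocation.
2. **Weeks 1 to 12.** The participant is told to use the watch whenever awake, every day.
3. **Week 12 visit.** The participant attends the laboratory in person while awake. The wearing instruction has no exception, and nothing says the watch has been handed back beforehand. A compliant participant therefore arrives with it.
4. **What the examiner can infer.** Under sections 2.4 and 2.4.2 only the experimental group is given a watch. Seeing the study device points to that group.
5. **Whether a safeguard intervenes.** Both safeguards concern what the participant says. Neither has the watch removed, covered or returned, and controls get no dummy device.
6. **Week 16 visit.** This is less certain. Taken literally, the instruction runs for the whole study, which includes week 16. It sits, however, within the description of a 12-week programme, and the protocol does not say when the watch is returned. Exposure at week 16 depends on whether the watch is kept.

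The outcomes then divide as follows.

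| Measure | How obtained | Exposed to an unblinded examiner? |
|---|---|---|
| Human Activity Profile: activity level, activity class, estimated cardiorespiratory fitness | Interview (sections 2.5.2) | Yes; one interview supplies all three |
| Stroke-Specific Quality of Life Scale | Interview (2.5.2) | Yes |
| Systolic and diastolic blood pressure | Aneroid device and stethoscope (2.5.2) | Yes; the examiner also works at the participant's arm |
| Perceived effectiveness | Answer recorded by the independent examiner (2.5.1) | Yes; this is listed among the primary feasibility measures |
| Self-efficacy scale | Ten yes/no items; mode of administration not stated | Unclear |
| Recruitment, retention, attendance | Ratios of counts (2.5.1) | Largely not |

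The wearing instruction and the blinding statement are thus each clear, but nothing in the protocol reconciles them for the week 12 visit.

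**The case against.** The strongest reply is that this is a 24-person feasibility study whose primary outcomes are mostly ratios and counts, which a visible wristband hardly touches. The questionnaires use fixed items and fixed answers: 94 items with three responses, 49 items scored five to one, and ten yes/no items. They are participants' own reports. Participants are unblinded in any case, and hiding the watch does not remove bias from that source. This stands as a limit on the consequence. It does not remove the gap, because interviews and manual blood pressure still leave the examiner some influence and the protocol itself claims blinding for them.

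Three stronger readings are tempting, and the document does not support them.

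- A reader might infer that blinding is lost at every follow-up assessment, with 12 of 12 experimental participants and 0 of 12 controls showing a device. That assumes full retention, full compliance and wear through week 16. It also assumes that no control owns a similar device, which the protocol does not rule out.
- A reader might infer that the Human Activity Profile scores will be biased upward in the watch group. That direction is plausible, but nothing in the document establishes the direction or the size.
- A reader might infer that the satisfaction item contradicts the request not to comment. Its wording is in Appendix 3, which is not available here, and both groups receive the same counselling programme, so rating it need not reveal the group. The related question that is visible, on perceived effectiveness, has seven closed answers and does not mention the watch.

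**Conclusion.** The point holds in limited form. Followed as written, the wearing instruction can reveal allocation to the examiner at week 12, and possibly at week 16 if the watch is kept, and no stated safeguard covers a visible device. This threatens the examiner-dependent measures and the between-group effect sizes intended for the later trial. One of those measures, perceived effectiveness, is a primary feasibility measure. The main feasibility counts are largely unaffected.

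The conclusion assumes that participants follow the instruction, that the watch is visible at the visit, and that the examiner recognises it as the study device. How many participants would be unmasked, and how far any estimate would shift, cannot be derived from the document.

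**What to change.** In sections 2.4.1 and 2.7:

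1. Tell experimental participants to take off the watch and keep it out of sight before they meet the examiner at weeks 12 and 16.
2. State whether the watch is returned at week 12 or kept until week 16.
3. Have the examiner complete the clinical measures before asking about satisfaction and perceived effectiveness, so that anything a participant lets slip there comes after those measures at that visit.

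The satisfaction and perceived-effectiveness questions should stay with the independent examiner. Passing them to intervention staff would conflict with section 2.5.1, which has the independent examiner record perceived effectiveness, and with section 2.7, which keeps the intervention team blind to participant data. Moving the diary hand-in would not help, since both groups keep a diary.

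The cost is a few sentences, a set order for the reassessment form, and a few hours of lost wear time on visit days. No extra staff are needed.
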